# A multi-centre, randomized, 3-month study to evaluate the efficacy of a smartphone app to increase caregiver’s positive mental health

**DOI:** 10.1186/s12889-019-7264-5

**Published:** 2019-07-05

**Keywords:** Study protocol, Clinical trial, Caregiver, Mobile phone application, Positive mental health, Mhealth

## Abstract

**Background:**

To assess the effectiveness of a smartphone app-based intervention compared to a regular intervention of caregivers in primary health care institutions. The intervention is aimed at increasing positive mental health and decreasing caregiver’s burden.

**Methods/design:**

Randomized and controlled trial with an experimental group and a control group. Subjects: 108 caregivers over 18, with a minimum of 4 months of experience as caregivers. Description of the intervention: an intervention with a smartphone app (*n* = 54) or a regular intervention for caregivers (*n* = 54). Each caregiver installs a smartphone app and uses it for 28 days. This app offers them a daily activity (Monday-Friday). These activities are related to the Decalogue of Positive Mental Health, which was designed ad hoc by a group of experts. The outcomes will be the score of caregiver burden, the positive mental health and participant satisfaction. These results will be assessed after the first, third and sixth month.

**Discussion:**

The results of this study will offer evidence of the effectiveness of an intervention using a free smartphone app. If its effectiveness is proven and the results are acceptable, this could lead to a rethinking of the intervention offered to caregivers in primary care.

**Trial registration:**

Clinical Register ISRCTN14818443 (date: 24/05/2019).

## Background

Increasingly, health needs have to do with age-related chronic diseases. The World Health Organization [1] highlights the trend of the aging population with more chronic diseases which makes necessary to carry out transverse, interdepartmental and integrated actions focused on disease prevention, health promotion and person-cantered care. Moreover, all these actions must be carried out with a community and population vision. According to the Catalan Health Plan 2016–2020 [2], it is necessary to establish dynamics of collaboration between services and professionals. To this end, a context with new health needs is proposed: on the one hand, the transformation of the healthcare system and, on the other, an orientation towards a more comprehensive care that focuses on the person and the value of life expectancy in good health.

Besides the increase of aging population there is an increase of caregivers. Those are exposed to the burden associated with their caregiving activities. In fact, the Catalan Health Plan 2016–2020 has already created a project named “Self-responsibility, self-care and promotion of the autonomy of people” and one of its aims is to promote the profile of the expert caregiver. According to Bauer and Sousa-Poza [3], the most evident affectation on the part of the caregiver is in relation to their quality of psychological health. The decrease of the psychological state has a direct impact on physical health. The authors pointed out that the profile of women, spouses, and intensive caregivers represent the prototype of a caregiver profile that is most affected by caregiving tasks.

The North American Nursing Diagnosis Association (NANDA) has been providing diagnoses associated with caregivers: D00061 Fatigue of caregiver role and D00062 Risk of fatigue of caregiver role. Anarte et al. [4] used these diagnosis to evaluate the process provided by the main caregiver of the dependent patients from a primary health centre from Castellon (Spain). In this study, 32 subjects were included. The results showed that 37,5% of them suffered from fatigues and 62,5% were under the risk of suffering fatigue. In their conclusions, they highlight that the main weakness of the caregiving process is related to the problems of communication between professionals regarding the care of caregiver.

A qualitative study that also explored caregivers’ role pointed out that caregivers sometimes even behaved against to their own state of well-being. The authors emphasize the need to develop interventions to support caregivers and improve their well-being [5]. This is what takes researchers like Ferré-Grau et al. to create intervention programs based on problem solving techniques related to prevent anxiety and depression [6].

As previously stated, some authors have already presented innovative proposals that include giving support to caregivers based on new technologies. As a matter of fact, Mckechnie et al. [7] evaluated a total of 14 empirical studies of computer-mediated interventions for informal caregivers of people with dementia. As a result of this systematic review, the authors support the provision of computer-mediated intervention for caregivers of people with dementia. However, they highlight that future interventions need to be under a study protocol involving a clinical trial with a control group.

“Mastery over Dementia” is an example of this. The authors of this Internet-based intervention focused on caregivers of patients with dementia. They designed and published the protocol of [8] an Internet-based course that includes eight sessions and a booster session over a maximum period of 6 month guided by a psychologist. The results [9] of this study showed that, with a sample of 149 caregivers, the intervention was acceptable. Another example is a web-based program for informal caregivers of persons with Alzheimer by Cristancho-Lacroix et al. [10]. However, their results show that it is desirable to create a more dynamic, personalized, and social intervention instead of a web-based intervention [11].

On the basis of this evidence, this study proposes to respond to the needs set out so far. Based on a previous project in which a website for caregivers was developed (www.cuidadorascronicos.com), a protocol to develop and evaluate a smartphone app-based intervention to promote positive mental health of caregivers is presented.

### Objectives

The objective of this study is to evaluate the effectiveness of a smartphone app-based intervention compared to a standard intervention of caregivers in primary health care institutions. The intervention is aimed at increasing positive mental health and to decrease caregivers’ burden.

## Methods/design

### Study design

Randomized, controlled trial with an experimental group and a control group (Participant Flowchart, Fig. 1).

**Fig. 1 Fig1:**
[figure not shown]
Participant Flowchart of the study

### Blinding

Blinding is impossible in this type of intervention. However, those responsible for.

data analysis will be blinded to group status.

### Participants and settings

Participants will be recruited from primary healthcare centres in 2 provinces of Catalonia (Tarragona and Barcelona). A randomly assignation will be done. Each primary healthcare centre that participates in this project will be provided with a copy of the study protocol.

#### Inclusion criteria

Primary / secondary and formal / informal family caregivers of people with chronic diseasesOver 18 yearsMinimum of 4 months of experience as caregiverKnowledge of Spanish or CatalanUse of a mobile device and WhatsAppAccess to a mobile device with Android as operating system and with Internet accessSignature of an informed consent

#### Exclusion criteria

Caregivers with cognitive impairment

### Sample size

Sample size was calculated considering to an alpha risk of 0,05 and beta risk of 0,2. Considering that, to get evidential data of the results, the sample should be of 54 subjects in each group with an estimated loss of 30% during follow-up and recognizing as statistically significant a difference greater than or equal to 10.

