### Outcomes

The primary outcome will be a change in positive mental health and caregiver burden at the first, third, and sixth month in the experimental group, compared to the control group.

The secondary outcome will be related to the adherence and satisfaction with the app: a) adherence to the intervention, measured by frequency of using the app; b) satisfaction with activities by the responses of usefulness of each activity; c) satisfaction with smartphone app in general reported by the satisfaction questionnaire.

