### Statistical analysis

The data will be analysed with SPSS version 22.0 (IBM CORP., Armonk, NY). Both groups results are going to be described by a descriptive analysis. Quantitative variables with a normal distribution will be described as means and standard deviation, or median and interquartile range otherwise, and qualitative variables as percentages and 95% confidence intervals. Possible baseline differences between trial arms will be statistically tested and further analyses will be adjusted for imbalances in the baseline scores. The primary analysis will be by intention to treat. For the primary outcomes, analyses will be corrected for multiple testing.

As sensitivity analyses, completers of all assessments will be analysed separately. Hypotheses tests will be performed at *α* = 0,05. The numeric outcomes will be analysed using analyses of variance; categorical outcomes will be analysed using *χ*^2^-tests.

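### The 80% power is stated at an unadjusted 0.05, but the primary outcomes are to be corrected for multiple testing, which leaves about 71% (two tests) to 55% (six, Bonferroni) per comparison

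*Protocol article*

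**What the plan says.** All references are to the protocol article.

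- **Sample size.** The section states "Sample size was calculated considering to an alpha risk of 0,05 and beta risk of 0,2". The other inputs are a 30% loss during follow-up and a single difference: "recognizing as statistically significant a difference greater than or equal to 10". The result is that "the sample should be of 54 subjects in each group". The section gives no SD, scale, month or multiplicity allowance.
- **Outcomes.** "The primary outcome will be a change in positive mental health and caregiver burden at the first, third, and sixth month", comparing the experimental with the control group. The two scales and three months are not ranked.
- **Statistical analysis.** "For the primary outcomes, analyses will be corrected for multiple testing". The method and the number of tests are not given. A later sentence says "Hypotheses tests will be performed at" alpha 0,05. Numeric outcomes are to be analysed by analysis of variance.
- **Data collection, Control group.** Both scales are completed at visit 1 (baseline) and again at visits 2 and 3, so two follow-up occasions are listed here against three in Outcomes.
- **Objectives.** The intervention is meant to raise positive mental health and to lower caregiver burden.

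**The concern.** The sample size and the primary analysis describe different tests. One alpha, one beta and one difference describe a single comparison at 0.05. The analysis involves at least two primary comparisons, one per scale, and up to six if each scale is tested at each month, with a correction that lowers the level of each test. A sample size that gives exactly 80% at 0.05 gives less than 80% per comparison at any stricter level. A later analysis plan can supply the correction method, but it cannot make a power stated at 0.05 hold at a smaller level.

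At stake is how a null result is read. If one scale shows no significant difference, readers will take it as coming from a trial with a 20% risk of missing a difference of 10, when the risk for that comparison may be 29% to 45%.

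**Working it through.** **Inputs from the protocol.** Alpha 0.05, beta 0.2, difference 10, 54 per group, 30% loss (Sample size); 1:1 allocation (Screening and randomization); two scales and three months (Outcomes).

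**Assumptions.** Two-sided tests; 54 per group delivers exactly 80% power at 0.05 before correction; Bonferroni as the reference correction.

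**1. The plan's own figure.** The 54 per group cannot be reproduced, because the SD is not given. Completers per group are 54 × (1 − 0.30) = 37.8, about 38. Solving the two-sample noncentral t power for the SD that gives 80% with 38 per group and a difference of 10 yields about 15.4. The normal approximation with 37.8 gives 10 / (1.960 + 0.842) × √(37.8 / 2) = 15.5. This SD is back-solved; it does not confirm the plan.

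**2. Number of primary tests.** One overall test per scale gives 2. Two scales at three months give 2 × 3 = 6. The Bonferroni levels are 0.05/2 = 0.025 and 0.05/6 = 0.00833.

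**3. Power per comparison at the corrected level.** Noncentral t, 38 per group, difference 10, SD 15.4:

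| Tests | Level per test | Power | Difference detectable with 80% power |
|---|---|---|---|
| 1 | 0.05 | 0.80 | 10.0 |
| 2 | 0.025 | 0.71 | 11.1 |
| 6 | 0.00833 | 0.55 | 12.6 |

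**4. Does the unknown SD matter?** Hardly. In the normal approximation, 80% at two-sided 0.05 fixes the expected test statistic at 1.960 + 0.842 = 2.802, whatever the SD or the way loss was allowed for. Power at a stricter level is Φ(2.802 − critical value):

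- two tests: Φ(2.802 − 2.241) = Φ(0.560) = 0.712
- six tests: Φ(2.802 − 2.638) = Φ(0.163) = 0.565

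If the calculation was one-sided, the figures are 0.701 and 0.537.

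**5. Size of the gap in participants.** Sample size scales with (critical value + 0.842)². For two tests the ratio is (3.083 / 2.802)² = 1.21; for six it is (3.480 / 2.802)² = 1.54. Restoring 80% per comparison by size would take about 46 completers (66 randomised) per group, or about 59 completers (84–85 randomised), against 54 randomised.

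**6. Holm in place of Bonferroni.** With two tests and a real effect on only one scale, power for that scale is about 71%. With the planned effect on both, power to show both is about 63% to 73% for correlations between the test statistics from 0 to 0.9. With an effect on every test and assumed correlations of 0.5 between scales and 0.6 between times, power per test is about 76% (two tests) or 67% (six).

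**The case against.** **The correction and test family belong in the analysis plan.** This stands for the method, the number of tests and the testing order; their absence from an article is no finding. It does not remove the mismatch, because the article itself states both the unadjusted sizing and the commitment to correct.

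**Multiplicity may already be allowed for.** Without an SD, a hidden allowance cannot be excluded. None is stated, and the only alpha given is 0.05. For the same reason, a reader should not infer that 54 is an arithmetic error: no stated sum is shown to be wrong.

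**Six tests is only one reading.** This is correct. Analysis of variance may give one overall test per scale, and the visit list suggests two follow-up occasions. A reader might infer that the type II error doubles; that holds only for Bonferroni over six tests (45% against 20%). With two tests it is 29%.

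**Winning on one comparison may be enough.** A reader might conclude that 80% power and a 5% family-wise error cannot coexist in this trial. That is too strong. With an effect on every test and the assumed correlations above, power for at least one win is about 85% (two tests) or 90% (six) with the error controlled. For two tests it runs from 92% at correlation 0 to 77% at 0.9. The protocol does not define success this way, however, and its objective names both scales.

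**The sentence on testing at 0.05 may look like a promise of uncorrected tests**, with a false-positive risk of up to 1 − 0.95⁶ = 26%. The text does not support this. The specific sentence requires correction for the primary outcomes, and 0.05 reads naturally as the overall level.

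**Conclusion.** The concern holds for power per primary comparison, and for power to show both scales. The stated 80% applies at an unadjusted 0.05, whereas the plan's own primary analysis uses a stricter level. If the 80% is granted at two-sided 0.05, power per comparison is about 71% with two tests and about 55% with six under Bonferroni; Holm loses less when all effects are real. The result barely depends on the unstated SD. It does depend on the number of tests and the correction, which the article leaves open.

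**What to change.** Choose one:

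- **(a)** Name one primary scale at one month, tested at 0.05. Test the second scale next in a fixed sequence and make the other times secondary. The 80% figure then matches the first test.
- **(b)** Keep both scales as primary at one named month, use Holm at an overall 0.05, and restate the power as about 71% per scale for a difference of 10. This is the worst case, when only one scale has an effect.

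In either case, say in Statistical analysis that 0.05 is the overall level for the primary outcomes, give the SD and the scale to which the difference of 10 refers, and reconcile the follow-up times in Outcomes with the visits in Data collection.

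The cost is wording in the protocol and analysis plan, with no extra participants. Under (a) the second scale can be claimed only after the first succeeds; under (b) the stated power is less favourable. The article describes the study as ongoing, so the change should be made before the data are analysed.

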### Screening and randomization

During the recruitment period, and until the calculated sample size has been achieved, participating care nurses who attend caregivers that meet inclusion criteria, will invite them to participate in the study (See Fig. 1). If the caregivers do not meet any exclusion criteria and agree to participate, the nurse will schedule a primary care visit (Visit 0, screening) with them.

Each participant will be assigned a code during the screening visit. The randomization unit will be the individual caregiver, assigned 1:1 to the experimental or control group. To generate the allocation sequence, the non-commercial Epidat 3.0 software will be used.

### Standard intervention for caregivers

Both study groups will receive the same standard nurse attention in primary healthcare which does not have any specific protocol. In regular attention, it is measured the caregiver burden using the scale Zarit [12] in its validation into Spanish [13].

#### Experimental group

The experimental group will receive the standard attention plus a free smartphone app. The app to be tested in the present trial has two different functions: a) an intervention in positive mental health; b) a link to an official website for caregivers. The website was developed in a previous project [14] and it is available at www.cuidadorascronicos.com.

The intervention has a duration of 28 days. During this period of time, the caregiver has the smartphone app active in his/her mobile device. Each day from Monday to Friday, the app offers him/her an activity. These activities are related to the Decalogue of Positive Mental Health by Lluch [15] which was designed ad hoc by a group of experts. After doing each activity, the caregiver can express if it has been useful or not. The app includes a motivational quote every day and it asks the caregiver “how do you feel”. During the weekend there are no activities, but the app recommends the caregiver to visit the abovementioned website. The last activity offers the caregiver the opportunity to register in this website. This allows him/her to be connected with other caregivers and to have access to any news published there.

#### Control group

Participants in the control group will only receive standard intervention for caregivers.

### Pilot test

It will be performed a pilot study with 15 participants in each group.

### Data collection

During visit 1, each participant will receive a specific dossier, which contains information about the study and their participation. There is one for the intervention group and another for the control group. The intervention group dossier includes information about the installation and information about the app. The control group dossier does not include this information. Both dossiers include information about each participation as it is explained bellow:

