#### Control group

In this first visit, the initial tests of control group must be answered. These tests include two sociodemographic questionnaires: a) about the caregiver – sex, birthdate, nationality, marital status, level of studies, health problems; and b) about caretaker – type of caretaker, birthdate and sex of the patient, his/her illness, hours of care, relationship between them, helpers in caregiving and emotions related on caregiving. It also includes the scale of positive mental health by Lluch [16], and the caregiver burden [13]. Both instruments will be used in visit 2 and 3.

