#### Experimental group

The experimental group has to answer questionnaires and scales as well as the control group. Besides, there is one extra questionnaire for visit 1 and visit 2. In visit 1, there is a questionnaire about the usage of technology. And in visit 2, a questionnaire about the app satisfaction.

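### The baseline scales share visit 1 with the arm-specific dossier, and nothing in the protocol ensures that they are completed before participants learn their arm

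*Protocol article*

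**What the plan says.** Under Screening and randomization, visit 0 is the screening visit. A code is assigned there; no outcome scale is listed, and the moment of randomization is not given.

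Data collection then describes visit 1: "During visit 1, each participant will receive a specific dossier, which contains information about the study and their participation". There are two versions: "There is one for the intervention group and another for the control group". Their content gives the arm away: "The intervention group dossier includes information about the installation and information about the app. The control group dossier does not include this information". The paragraph closes by saying that both dossiers tell participants what taking part involves, and leads straight into the tests, set out arm by arm.

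For controls, "In this first visit, the initial tests of control group must be answered". These tests comprise the sociodemographic questionnaires, the positive mental health scale and the burden scale. For the other arm, "The experimental group has to answer questionnaires and scales as well as the control group". That arm has more to fill in: "Besides, there is one extra questionnaire for visit 1 and visit 2". The extra form at visit 1 concerns use of technology.

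The Blinding section says "Blinding is impossible in this type of intervention" and promises only that the data analysts will not know the groups. Outcomes defines the primary outcome as change in the two scales. Statistical analysis provides for testing baseline differences and adjusting later analyses for imbalances in baseline scores.

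**The concern.** A baseline score is useful in a randomized comparison because allocation cannot have affected it. Any difference between arms is then due to chance, and adjusting for it can only help. If participants know their arm when they answer, that property is lost. Someone who has just been given an app, or has just learned that they will not get one, may rate their mood or burden differently as a result.

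Both scales are self-reported, so the participant is the assessor. Follow-up in a trial of an app is unavoidably open, and the Discussion admits this as a limitation. An open baseline is avoidable, and the article neither prevents it nor acknowledges it. Blinding the analyst does not help, because the shift would already be in the recorded answers. At stake is an avoidable bias in the primary effect estimate for both scales.

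**Working it through.** The plan gives no figure on this point. Its one computed figure, 54 per arm, does not enter the argument. The check is a comparison of sections in visit order, followed by the algebra of what a shifted baseline does.

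**Sequence**

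1. Visit 0 (Screening and randomization): code assigned, no scale listed.
2. Visit 1 (Data collection): the arm-specific dossier is handed over. This requires that allocation has been made by then.
3. Visit 1 (Data collection, Control group): both scales are answered. The same paragraph says that the two instruments are used again at visits 2 and 3, so the first visit there is visit 1.
4. Visit 1 (Data collection, Experimental group): the same scales, plus a technology form for this arm only.
5. No section states whether the scales or the dossier come first, or when the allocation is disclosed.

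Steps 2 to 4 establish that allocation precedes or coincides with the baseline visit, and that arm-revealing material is used at that visit. The text order, with the dossier leading into the tests, points to dossier first but does not say so. The burden measurement in regular care (Standard intervention for caregivers) is not described as the trial baseline, so it does not supply a pre-allocation score.

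**Effect on the estimate**

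Let τ be the true effect at follow-up. Let b be the difference between arms (app minus control) in recorded baseline caused by knowing the arm, and β the within-arm slope of follow-up on baseline. Assume that the shift affects only the baseline answers and has gone by follow-up.

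- Change-score comparison: expected value τ − b, so the bias has size b.
- Baseline-adjusted comparison: expected value τ − βb, so the bias has size βb.

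The document gives neither b nor β. For assumed slopes of 0.3 to 0.7:

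- b = 1 point: bias 1 point for the change score; 0.3 × 1 = 0.3 to 0.7 × 1 = 0.7 after adjustment.
- b = 5 points: bias 5 points for the change score; 0.3 × 5 = 1.5 to 0.7 × 5 = 3.5 after adjustment.

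These values show the mechanism only. Adjustment shrinks the bias but does not remove it.

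**Direction**

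The sign of b is open. On positive mental health, hope in the app arm or disappointment among controls gives b > 0 and understates the benefit. If app recipients stress their need for help, b < 0 and the benefit is overstated.

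**The case against.** The strongest reply is that the order within the visit is inferred. A nurse could collect the scales first and then hand over the dossier, and every sentence in the article would still be true. The article is condensed, its flowchart is not shown, and the order of forms within one visit is detail that a full protocol may hold. A nurse who knows the arm is also not the same as a participant who knows it. This stands to the following extent: a reader might infer that participants already know their arm when they answer the baseline scales, and the document does not state that. What remains is that the article itself fixes allocation, arm-specific material and self-reported baseline at one visit, and names no safeguard. That goes beyond an omitted detail.

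A reader might also infer that people who withdraw on learning their arm would lack a baseline score and so weaken the intention-to-treat set. The document does not support this. The only step described as revealing the arm to participants is at the visit where baseline is collected, so withdrawal after that visit leaves a baseline score.

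It is also true that the Discussion concedes that the open design could introduce bias. That concession is general and does not address baseline timing. Finally, the technology form given only to the app arm does not itself bias the primary scales. It matters here only as a further sign that the arm is in play at visit 1, and there is no stated analysis that would need it from controls.

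**Conclusion.** The point holds as a weakness in the described sequence, not as proof that the baseline is contaminated. Allocation exists by visit 1, arm-revealing material is given at that visit, both primary-outcome scales are answered at it, and nothing shown keeps knowledge of the arm from the answers. Dossier first is a well-supported reading, not a stated fact.

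The size and direction of any bias cannot be determined. It is tempting to express it as a share of the 10-point difference in Sample size, but the article does not say which scale that difference refers to and gives no basis for the size of the shift, so no percentage is warranted. The conclusion rests on two assumptions: that the order within the visit is not fixed elsewhere with the scales first, and that knowing the arm can move self-reported answers. If the full protocol already puts the scales first, a clarifying sentence settles the matter.

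**What to change.** State in Data collection that all participants complete the sociodemographic forms and both scales at visit 0, or at the start of visit 1, before the allocation is opened. Only once these forms are returned is the allocation opened and the arm-specific dossier handed over, followed by the technology questionnaire in the app arm. State the moment of randomization in Screening and randomization so that the two sections agree. As the study is reported as ongoing, also record which order was used for participants already enrolled.

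The cost is a re-ordering of steps at an existing visit and a short clarification of the protocol. It needs no extra visit, participants or forms, and no change to the analysis.
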